##### Post-dosing Phase

Visit 10 (Day 104; End of study).

Participants will return to the research laboratory for final testing, which will include collection of blood and saliva samples, completion of biopsychological and health questionnaires, and neuro-physiological and physiological laboratory tests. This testing session will help us to re-assess participants to determine the manner in which the study product remains in their body, as shown by their blood results, after terminating its use. Logbooks will be collected at this time.

### Withdrawal criteria

Study participants may withdraw from the study at any point. Participants will be withdrawn if they suffer from any intolerable adverse effects resulting from the CBD intervention, if they fail to attend required site visits, or they are noncompliant with the CBD dosing regimen. For transparency, though, all participants withdrawn from the study will be included in the final report.

### Sample size justification and statistics

Due to the limited research available, we will assume a 0.5 correlation between 10 successive data time points. To detect a 0.25 moderate effect size in cardiovascular metrics (blood pressure and heart rate variability) with 90% power and 95% confidence, 36 total participants are required. To account for dropout and non-compliance rates, 15–20% more participants will be recruited in each study. Statistical analysis will be performed using IBM® SPSS® Advanced Statistics, and a combination of statistical analyses will be used depending on the outcome variable. In general, multiple repeated multilevel linear mixed models will be used with statistical significance set at p ≤ 0.05.

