**Methods/design:**

Forty participants will receive escalating doses of CBD ranging from 5 mg CBD/kg/day to 30 mg CBD/kg/day. The CBD dose is escalated every two weeks in increments of 5 mg CBD/kg/day. Participants will provide blood for pharmacological assessments at each of the 10 visits. Participants will complete a physiological assessment at each of the visits, including assessments of cerebral hemodynamics, blood pressure, electrocardiogram, seismocardiogram, transcranial magnetic stimulation, and salivary analysis for genomic sequencing. Finally, participants will complete a psychological assessment consisting of sleep, anxiety, and pain-related questionnaires.

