### Study population

We will recruit 40 participants across two study sites. Eligibility to participate in the study include the following criteria:Healthy male adults between 18–35 years of age that compete (in any level, including recreational, collegiate, professional) in contact sport athletics (including American football, soccer, rugby, wrestling, and hockey).Non-smokers without known medical complications.Ability to maintain commitment to all proposed biopsychological and health questionnaires, and neuro-physiological and physiological laboratory tests.

Participants meeting any of the following criteria are excluded from the study:

Currently under treatment (e.g., by a physician or clinical psychologist) for anxiety, depression, post-traumatic stress disorder, mood disorder, psychotic disorders or any cerebrovascular and cardiovascular complications.Unable to maintain commitment to all proposed biopsychological and health questionnaires, and neuro-physiological and physiological laboratory tests.

Since the study is employing a continuous dose escalation design, a placebo-washout design will be implemented. All participants will first intake a placebo for 2 weeks prior to beginning their CBD dosing protocol. As such, no participant randomization of participants will occur, and neither the study participants nor the study investigators will be blinded to the CBD dose. As we will likely recruit the majority of the participants from the university population, they are expected to be in their off-season.

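### The 40 planned recruits are 11% above the required 36, not the stated 15–20% (42–44), and allow for at most 10% loss

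*Protocol article*

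**What the plan says.** The section Sample size justification and statistics in the protocol article sets out the calculation in three steps.

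- Assumptions: "we will assume a 0.5 correlation between 10 successive data time points", and "To detect a 0.25 moderate effect size in cardiovascular metrics (blood pressure and heart rate variability").
- Result: "with 90% power and 95% confidence, 36 total participants are required".
- Allowance for losses: "To account for dropout and non-compliance rates, 15–20% more participants will be recruited in each study".

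The recruitment figure appears elsewhere. Study population says "We will recruit 40 participants across two study sites", and the abstract's Methods/design paragraph says "Forty participants will receive escalating doses of CBD".

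For the analysis, the same section says that "multiple repeated multilevel linear mixed models will be used", with "statistical significance set at p ≤ 0.05".

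**The concern.** Three figures are printed: a requirement of 36, an overage of 15–20%, and recruitment of 40. They cannot all be right, because 36 increased by 15–20% does not give 40 under any rounding.

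The allowance is there to keep the number of completers at or above 36. The Withdrawal criteria section provides for removal because of intolerable adverse effects, missed visits or non-compliance, and the schedule has ten visits from Day -15 to Day 104. Some loss is therefore to be expected. If losses reach the level that a 15–20% overage is sized for, the trial ends with fewer participants than its own stated requirement. A reader relying on the sample-size section would believe in a margin that the recruitment figure does not provide.

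**Working it through.** **Inputs (protocol article).** Required N = 36, power 0.90, alpha 0.05, effect size 0.25, correlation rho = 0.5, m = 10 time points and overage 15–20% (Sample size justification and statistics). Recruitment 40 (abstract; Study population). One group, no randomisation (Study population). The effect-size measure is not named; 0.25 is taken as Cohen's f, which is an assumption.

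**1. Overage against recruitment.**
- 36 × 1.15 = 41.4 and 36 × 1.20 = 43.2, so 42–44 recruits.
- 40 / 36 = 1.111, an overage of 11.1%.
- Shortfall against the stated rule: 42 − 40 = 2 to 44 − 40 = 4 recruits.
- Loss that 40 can absorb while keeping 36: 1 − 36/40 = 10%.

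**2. Completers at the loss the overage is meant to cover.**
- An overage of 15% covers a loss of 1 − 1/1.15 = 13.0%; an overage of 20% covers 1 − 1/1.20 = 16.7%.
- 40 / 1.15 = 34.8 and 40 / 1.20 = 33.3, so about 33–35 completers.

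**3. Can the stated 36 be reproduced?** For a one-group repeated-measures F test, the noncentrality is λ = N·m·f²·ε/(1 − rho), with degrees of freedom (m − 1)ε and (N − 1)(m − 1)ε. Here ε is the sphericity correction, equal to 1 under sphericity.
- With every stated input and ε = 1, N = 17 gives λ = 17 × 10 × 0.0625 / 0.5 = 21.25 and power 90.4%. The required N is therefore 17, not 36. At N = 36, λ = 45 and power exceeds 99.9%.
- N = 36 comes out with m = 3 in place of 10 (λ = 36 × 3 × 0.0625 / 0.5 = 13.5; power 90.6%), or with m = 10 and ε = 1/3 (λ = 15; power 90.6%).
- A convention that leaves rho unused, λ = N·f²·(m − 1) with m = 10, gives λ = 36 × 0.0625 × 9 = 20.25 and power 89.8% at 36. It reaches 90% at N = 37.

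**4. Power at 33–35 completers under each reading.**

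| Reading | N = 33 | N = 34 | N = 35 | N = 36 |
|---|---|---|---|---|
| All stated inputs, ε = 1 | 0.999 | 0.999 | 0.999 | 0.999 |
| m = 3, rho 0.5 | 0.878 | 0.888 | 0.898 | 0.906 |
| m = 10, rho 0.5, ε = 1/3 | 0.876 | 0.887 | 0.897 | 0.906 |
| m = 10, rho unused | 0.864 | 0.876 | 0.888 | 0.898 |

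Each of the last three rows either needs a value that the protocol does not state or leaves a stated one unused.

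**The case against.** Two stronger conclusions are tempting, and the protocol supports neither.

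The first is that the sponsor expects 15–20% dropout, which would leave 40 × 0.80 = 32 to 40 × 0.85 = 34 completers. No dropout rate is stated anywhere. The 15–20% is extra recruitment, which corresponds to 13.0–16.7% loss and about 33–35 completers.

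The second is that the stated 90% power will not be met. That follows only if 36 is taken as the true requirement. On the stated inputs 36 is far more than needed, and 33–35 completers keep over 99% power. Even on the readings that make 36 roughly a 90% figure, the drop from 36 to 33 is at most about 3.4 percentage points (0.898 to 0.864).

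Two further points soften the consequence. The planned linear mixed models can use visits completed before withdrawal, so counting completers understates the information available. This helps least at the highest doses, because everyone escalates in the same order and those who leave early contribute nothing there. Also, the calculation is for cardiovascular measures, whereas the Discussion names the pharmacokinetic data as the primary outcome.

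These arguments stand and limit the severity. They do not remove the mismatch: the protocol cannot rely on a smaller requirement while stating that 36 are needed, and 40 is not 15–20% above 36.

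**Conclusion.** The point holds as an inconsistency between printed figures. The stated rule calls for 42–44 recruits and the plan has 40, which is 2–4 fewer. Forty is an 11.1% overage and covers at most 10% loss. At the loss a 15–20% overage is sized for, about 33–35 participants would complete, which is 1–3 below the stated 36. This part is arithmetic on the protocol's own numbers and needs no assumption.

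The effect on power is undetermined. It is nil in practice on the stated inputs (over 99%, with 0.25 as Cohen's f and sphericity), and power is about 0.86–0.90 on readings under which 36 is roughly a 90% figure. The text does not say which calculation produced 36. The severity is minor to moderate: wrong as written and worth correcting, but no threat to the trial's main pharmacokinetic aim.

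**What to change.** Keep recruitment at 40 and amend the sample-size section in two respects.

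1. Replace the 15–20% overage with wording such as: about 11% more participants will be recruited (40 in total), which allows for up to 10% loss while retaining 36.
2. Give the power at about 33–36 completers from the calculation actually used for 36, and name its effect-size measure, number of time points and sphericity assumption.

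The cost is a sentence or two of text. No additional participants and no change to study conduct are needed. Depending on the calculation used, the power reported at 33–35 completers may be slightly below 90%, or well above it.

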### Physiological and psychological testing

Venous blood samples will be taken at each visit to monitor the safety of the cannabinoid intervention in each study and/or to conduct pharmacological assessments. A licensed medical laboratory technician will complete a blood draw via venipuncture from the cubital fossa. The blood samples will be analysed by an accredited provincial laboratory for basic hematological and clinical chemistry parameters, and by the [name] laboratory in the College of Pharmacy & Nutrition at the University of Saskatchewan for quantitative determination of cannabinoid plasma levels. This laboratory will also conduct the analysis of biomarkers using commercially available kits.Blood collected in a lithium heparin tube will allow for assessment of CBD and Δ^9^-THC concentrations and their active metabolites. These will allow us to study the pharmacokinetics and determine the relationship among plasma levels, efficacy and side effects.Blood collected in a serum separating tube will allow for assessment of biomarkers that include Tumor Necrosis Factor alpha (TNF-alpha), brain-derived neurotrophic factor (BDNF), Interleukin-6, and C-reactive protein. These markers will complement our physiological parameters and will be analyzed using immunoassay ProcartaPlex™ kits performed on a Luminex™ platform (Life Technologies, Frederick, MD) as per other studies [29].Blood collected in a lithium heparin tube will allow for genome-wide sequencing analysis for single nucleotide polymorphisms and copy number variants (*e.g.* CNVs for cannabinoid-metabolizing enzymes such as cytochrome P450 2D6 *CYP2D6*) (Next Generation Sequencing Laboratory, University of Saskatchewan, Saskatoon, Saskatchewan, Canada).For initial risk assessment and safety, blood collected in a serum-separating tube and EDTA tube will be analyzed at the Regina General Hospital laboratory for assessment of complete blood count (CBC) and differential, and assessment of general chemistry (such as liver enzymes).

All blood tubes are 4–6 mL each. A small amount of the blood will be kept frozen for future research related to this study if participants indicate agreement on the consent form. In addition to the blood samples, saliva samples will be collected. This will allow for DNA analysis for metabolic genes [30], and will be analyzed by My Next Health Inc. (Oakville, Ontario, Canada). The salivary are processed through an automated DNA Extraction Pipeline. After extraction is completed, each sample undergoes’ genomic DNA quality control, and the passing samples proceed to sample preparation. Sample preparation converts a sample into a library of fragments which is sequenced on a Next-generation sequencing (NGS) instrument. The Nucleotides are “read" on the Illumina NovaSeq 6000 sequencer at an 80X depth/read number to ensure appropriate accuracy. Finally, the genes and gene variants are called using the Illumina DRAGEN pipeline and confirmed by the My Next Health (https://mynexthealth.com) data-driven QAQI analysis.

### Sleep quality assessment

As sleep quality and sleep efficiency (time actually asleep compared to time in bed) are also altered following a sport-related concussion [31, 32], and in those with persisting post-concussion symptoms/symptomology (PPCS) [33], all participants will be given an actigraph (Phillips Respironics, Actiwatch) to wear to bed each night. The actigraph records details about sleep, such as time spent in bed, time spent asleep, and wake after sleep onset. Furthermore, participants will complete the Leeds Sleep Evaluation Questionnaire at each laboratory visit [34]. Research pertaining to the influence of CBD and ∆^9^-THC on sleep is still in its infancy, however, there is still some evidence available to show improvements in sleep quality following administration of these cannabinoids [35].

### Protocol

#### *(1) **Cerebrovascular and cardiovascular protocol*

Each study will require participants to complete this “Neary” protocol [36] to understand how their cerebrovascular and cardiovascular function are affected by intake of the cannabinoids. Prior to testing, participants will be asked to refrain from consuming any alcohol for 24 h, from exercising for 12 h before, and from consuming caffeine for 6 h [37]. The participants will be encouraged to eat a small meal at least 2 h before testing and asked to void their bladder within 30 min of arrival. Participants will be attached to the following equipment: bilateral transcranial Doppler to measure blood flow velocity of the brain [19, 38], Functional near infrared spectroscopy (fNIRS) – fNIRS to measure oxygenation of the brain [13], and a Finapres Nova to record electrocardiogram and blood pressure continuously via finger photoplethysmography. The Finapres has a 5-lead ECG to record heart rate and the electrocardiogram [36, 39], a mouth-piece connected to a gas analyzed to collect expired carbon dioxide and oxygen [40], and a seismocardiograph to record cardiac cycle timing intervals and contractile parameters [12, 41]. After participants are attached to the equipment, they will complete the following protocol:

1) 30-min supine rest to establish spontaneous physiological baseline [42]This protocol can provide insights associated with different peak activity intensities within six frequency intervals, each of which is associated with the following physiological functions: cardiac interval (0.6–2 Hz), respiratory interval (0.145–0.6 Hz), smooth muscle cell activity interval (0.052–0.145 Hz), autonomic innervation of smooth muscle (0.021–0.052 Hz), endothelial function related (0.0095–0.021 Hz), and nitric oxide dependent (0.005-0.0095 Hz) intervals. The activity intensities of cerebral blood flow velocity, blood pressure, and fNIRS parameters will be calculated at each interval during the 30-minute supine rest. This allows for analysis of resting state networks, such as the default mode network. During the first minute, the seismocardiograph recording (i.e., seismocardiogram) will be completed.

2) Six-breaths/minute paced breathing maneuver repeated for 5-min [18]A 6-breaths per minute pace has been shown to allow for comparable measurements of autonomic function, including heart rate variability, baroreflex sensitivity, and blood pressure variability, and allows for a similar adaptation of respiratory sinus arrhythmia during each assessment.

3) Two-minute washout period to re-establish baseline physiology.

4) Squat-stand baroreflex maneuver (10 s squat:10 s stand, repeated 5-min) to assess flow-pressure reactivity and dynamic cerebral autoregulation.Repeated squat stands is a useful method of assessment of dynamic cerebral autoregulation. This method have been used to study parasympathetic baroreflex responses, blood pressure alleviation, cerebral oxygenation, and cerebral blood flow responses [15, 43–45].

This complete protocol will take ~ 45 min.

#### *(2) **Neurophysiological assessment protocol*

Transcranial magnetic stimulation (TMS) – TMS will be used to assess δ-aminobutyric acid (GABAergic) inhibition in the primary motor cortex [46, 47]. TMS will be delivered with a figure-eight coil and guided by neuro-navigation software to target the cortical motor representation for the first dorsal interosseous muscle of the dominant hand, from which surface electromyography (EMG) will be recorded. Standard procedures will be followed to identify the corresponding hotspot, and resting and active motor thresholds (rMT, aMT). To evaluate cortical inhibition, two TMS measures will be obtained: the cortical silent period (CSP) and short-interval intracortical inhibition (SICI). To elicit the CSPs, single-pulse TMS will be delivered at 120% of aMT while participants maintain a pinch grip contraction generating 20% of maximum voluntary contraction force. The duration (ms) of the transient quiescence in EMG activity following the motor evoked potential will be measured as the CSP. To assess SICI, we will deliver paired-pulse TMS. In this protocol, a sub-threshold conditioning stimulus will precede a supra-threshold ~ 1 mV amplitude test stimulus by 2 ms. The reduction in amplitude of the test stimulus when ‘conditioned’ by the preceding stimulus will be measured as SICI. To ensure valid comparison of paired-pulse measures across different time-points, where necessary we will adjust the test stimulus, so that test MEP sizes will be matched to within 30% of the comparison time-point. For each of the aforementioned measurements, 20 pulses of TMS will be delivered with inter-stimulus intervals of 5–8 s.

This protocol will take approximately 30 min to complete.

#### (3) Health questionnaires and nonverbal pain behavior

A key component of our analysis is the impact of our CBD administered continuously on normal psychological function. Thus, a number of health questionnaires will be administered to assess mental health over the duration of the study. These will include an initial medical history (including medication information) form, the Health-related quality of life (HRQOL), the Generalized Anxiety Disorder (GAD-7) Questionnaire, the Brief Pain Inventory-Short Form (BPI-SF), McGill Pain Questionnaire-Short Form (MPQ-SF), Numeric Rating Scale for Pain (NRS), and Genotype/phenotype Questionnaire. Complementing this self-report, we will use a validated Pain Behaviour Measurement system (PBM) [48] to capture non-verbal pain expressions during movement, where applicable [49]. Additionally, we will complete the sport concussion assessment tool 6 (SCAT6) symptom checklist at each visit, which includes extensive details pertaining to previous history of concussion on the initial intake.

Our assessment approach is consistent with the Initiative on Methods, Measurement, and Pain Assessment in Clinical Trials recommendations [50, 51] and involves assessment tools that are widely validated across pain types and populations.

#### (4) Pharmacokinetic assessment

This assessment aims to determine whether a correlation exists between dose, steady-state trough concentrations (C_SS,Min_), and/or pharmacodynamic assessment for the cannabinoids and their active metabolites. To draw such correlations, blood samples must be collected just before a dose administration when the concentrations are at steady state. Plasma levels of CBD and its metabolites will be assessed using a previously described validated Liquid Chromatography-Mass Spectrometry (LC–MS/MS) method with minor modifications [52]. Heparinized lithium Barricor vacutainers ® (BD Canada, Mississauga, ON) will be used to collect blood samples from the study participants [53]. Following collection, venous blood will be centrifuged at 1500 rpm for 10 min, and plasma transferred to LoBind microcentrifuge tubes and stored at − 80 °C until analysis.

The validated LC–MS/MS method can quantify plasma concentrations of THC and CBD and their active metabolites, 11-OH-THC and 7-OH-CBD, respectively. Stock solutions (in methanol) of 1 mg/mL of cannabinoids and respective stable isotope-labeled internal standards (Cerilliant Corp., Round Rock, TX) will be stored at -20 °C until use. To create a calibration curve, the stock solutions will undergo serial dilutions using blank human plasma. Low, medium, and high concentration Quality Control standards (two at each level) will determine the acceptance criteria for the analytical run, and will be incorporated into each analytical run of participant samples. A plot of the peak area ratios of the cannabinoid and its respective internal standard against the nominal concentration will construct the calibration curve. A linear least-squares regression analysis using 1/X as a weighting factor will determine the linearity of the calibration curves with requirement that all calibration curves have a coefficient of determination (r^2^) > 0.99. Intra- and inter-day precision and accuracy will also be within 15%, except at the limit of quantification that will be within 20%, and all Quality Control samples for a given run will be within 15% of their nominal values. Preparation of participant plasma samples will involve addition 200 μL cold acetonitrile and 10 μL internal standard working solution, followed by vortex-mixing and centrifugation for 10 min at 20,000 g while maintaining a temperature of 4 °C. Supernatant will be transferred to borosilicate tubes and dried under filtered air for 30 min at 37 °C. Samples will be reconstituted with 200 μL mobile phase and 100 μL transferred into HPLC inserts.

Quantification of the cannabinoids will be performed using an Agilent 1290 binary pump LC system with an online degasser (Mississauga, ON) coupled to an ABSciex 6500 triple quadrupole mass spectrometer with TurboSpray ionization (Concord, ON). 5 μL will be injected onto a Zorbax Eclipse XDB-C8 narrow bore (2.1 × 12.5 mm, 5 μm) guard column and Zorbax Eclipse XDB-C18 small-bore (2.1 × 12.5 mm, 5 μm) column while maintaining the column temperature at 30 °C to separate the cannabinoids. Mobile phase A (water containing 0.1 mM ammonium formate) and B (methanol containing 0.1 mM ammonium formate) at a flow rate of 250 μL/min and a 10 min gradient will separate the cannabinoids. Positive ion mode electrospray ionization (ESI), with an ion spray voltage of 5500 V, will be used to conduct multiple reaction monitoring (MRM) for quantification of CBD (quantifier ion m/z 315.1 > 193.2; qualifier ion m/z 315.1 > 259.2), THC (quantifier ion m/z 315.1 > 193.1; qualifier ion m/z 315.1 > 259.2), 11-OH-THC (quantifier ion m/z 331.1 > 193.1; qualifier ion m/z 331.1 > 201.0), CBC (quantifier ion m/z 315.1 > 193.2; qualifier ion m/z 315.1 > 259.2), CBD-d3 (318.2 > 196.1), THC-d3 (318.2 > 196.1), and 11-OH-THC-d3 (334.2 > 196.1) using a ABSciex 6500 QTRAP mass spectrometer (ABSciex, Concord, ON, Canada) and MultiQuant 3.0.1 Software. The temperature, gas source 1, gas source 2, curtain gas, entrance potential, and collision activated dissociation gas were set to 600 °C, 70, 60, 50, 10 V, and 10, respectively. The samples will be analysed in batches within three months of collection as excellent stability has been confirmed only for up to 3 months when stored at -80 °C [52].

